#### Termination Criteria

Discharge in a stable condition with advice.

#### Exit Criteria

Death or discharge before total enteral nutrition.Guardian request to withdraw from the study.Sepsis, NEC, use of ventilatory support, or critical illness is not suitable for continuing to participate in the study.

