### Sample Size

This is a prospective randomized controlled study. Patients meeting the inclusion and exclusion criteria are randomly divided into two groups, group A (AAF) and group B (EHF). Time to reach full enteral feeding is the primary outcome measure; the same research is unreported at present. According to Raimondi's study (15) and experience in clinical practice, the mean time to full enteral feeding in group A is 23.6 ± 15.6 days, accounting for a 30% disparity, the time to full enteral feeding between the two groups differs by approximately 7.08 days. Hypothesis tests are two-sided with a significance level of 5%, while the statistical power is set at 80%. In this study, Zα = 1.96, Zβ = 0.84, σ represents standard deviation, δ represents the difference between the mean values in the two groups, and the formula for calculating sample size is as follows:

$$\begin{array}{l} n=\frac{{\left(Z_{\alpha }+Z_{\beta }\right)}^{2}*2\sigma^{2}}{\delta^{2}} \end{array}$$

After calculation, a sample size of 76 per group is required, accounting for a 20% miss rate. Ninety-five patients per group need to be included, and the planned sample size of this study is at least 190 patients in total.

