### Outcome

#### Primary Outcome

Time (days) to reach full enteral feedings, defined as a daily intake of ≥ 150 mL/Kg/day for 3 days in a row (age at the first day of achieving full enteral feedings as the indicator).

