### Statistical Analyses

The statistical analysis is performed using the SPSS software package, version 22.0. The measurement data obeying the normal distribution are expressed as x ± s, and the *t-*test is used for comparison between groups. Non-normally distributed continuous variables are expressed as median with interquartile range and compared using the Mann-Whitney U test. The enumeration data are expressed by rate (%) and analyzed by the chi-square test or Fisher's exact test. *P* <0.05 is considered a significant statistical difference.

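### Randomised infants leave the study for illness, death or discharge before full feeding, so the primary comparison is open to selection bias of unknown size and direction

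*Protocol article*

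**What the plan says.** All references are to the protocol article.

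- **Exit Criteria.** Three reasons are listed: "Death or discharge before total enteral nutrition"; a guardian's request to withdraw; and "Sepsis, NEC, use of ventilatory support, or critical illness is not suitable for continuing to participate in the study". Apart from the guardian's request, all are clinical events or discharge after randomisation.
- **Primary Outcome.** Time to full enteral feeding, "defined as a daily intake of ≥ 150 mL/Kg/day for 3 days in a row", with age on the first such day as the value. An infant who never gets there, or is no longer observed, has no value.
- **Statistical Analyses.** A t-test if the data are normal; otherwise, "Non-normally distributed continuous variables are expressed as median with interquartile range and compared using the Mann-Whitney U test". No other method is given for a continuous outcome.
- **Sample Size.** "a sample size of 76 per group is required, accounting for a 20% miss rate"; this becomes 95 per group, 190 in all.
- **Secondary Outcome.** The study endpoint is the day of discharge. Adverse events are a secondary outcome, and Table 1 marks them at discharge only.

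The article does not say whether infants who exit are followed, or how they are scored in the primary comparison.

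**The concern.** Randomisation makes the two groups comparable at entry. That protection is lost if infants drop out of the comparison because of what happens afterwards, when those events relate to the outcome and may depend on the allocated formula.

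The article supplies both links. Its Background says feeding intolerance delays full enteral nutrition and so raises the risk of infection. Its Discussion says AAF may reduce nosocomial infection. Under Feeding Schedule, abnormal abdominal findings stop feeds, and persistent residuals prompt tests to rule out NEC and severe infection. Infants who exit may therefore be the slow feeders, and their number may differ by formula.

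If one formula led to more such exits, its remaining infants would look faster. If AAF prevented infection, EHF would lose more of its slow feeders and part of AAF's benefit would be hidden. An infant who exits with NEC or sepsis may also go uncounted among the adverse events, since these are recorded at discharge.

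**Working it through.** **1. The plan's own figure.** Inputs from Sample Size: mean 23.6 and SD 15.6 days in the AAF group, a 30% difference, two-sided 5%, power 80%.

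- δ = 0.30 × 23.6 = 7.08 days.
- n = (1.96 + 0.84)² × 2 × 15.6² / 7.08² = 76.13, given as 76 (77 if rounded up; immaterial here).
- 76 / (1 − 0.20) = 95 per group, 190 in total. The stated figures reproduce.
- Budgeted loss: 0.20 × 95 = 19 per group, 38 of 190.
- For a 7.08-day difference and SD 15.6, power is 79.9% with 76 per group and 87.9% with all 95.

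**2. What informative exit could do.** The documents give no exit rates by group and no relation between illness and feeding time, so these are assumptions:

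- Times are lognormal, AAF mean 23.6 and SD 15.6. The SD of log time is s = √ln(1 + (15.6/23.6)²) = 0.602.
- EHF times are either the same (no effect) or 1.3 times as long (mean 30.68; true difference 7.08).
- Each infant has a latent sickness score with correlation ρ to log time. A proportion p with the highest scores exits without a primary value.
- Exits average 20%, as in the plan.

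The mean time among infants who remain is k × 23.6 × Φ(c − ρs) / (1 − p), where c is the (1 − p) normal quantile and k is 1 or 1.3.

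Example with ρ = 0.5, a true effect, and exits of 10% (AAF) and 30% (EHF):

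- AAF: 23.6 × Φ(1.282 − 0.301) / 0.90 = 23.6 × 0.8366 / 0.90 = 21.94 days.
- EHF: 30.68 × Φ(0.524 − 0.301) / 0.70 = 30.68 × 0.5884 / 0.70 = 25.79 days.
- Difference 3.85 days instead of 7.08.

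The table gives the range from ρ = 0.3 to ρ = 0.8. False-positive rates are for the Mann-Whitney test on infants with a value, simulated with 95 randomised per group and no true difference (3,000 replicates).

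| Exits AAF / EHF | Observed difference when the truth is 7.08 days | False-positive rate with no true difference |
|---|---|---|
| 20% / 20% | 6.6 to 5.7 | about 5% |
| 15% / 25% | 5.9 to 3.9 | about 5 to 12% |
| 10% / 30% | 5.1 to 2.0 | about 8 to 38% |
| 30% / 10% | 8.1 to 9.4 | mirror image of the row above |

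If exit is unrelated to feeding time (ρ = 0), the difference stays at 7.08 days whatever the exit rates, and the false-positive rate is about 5%.

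**3. Reading the table.** False positives need both unequal exit and a link to feeding time. With a real effect, equal exit already shrinks the observed difference. The direction of the error depends on which group loses more infants.

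**The case against.** **No bias is shown.** A reader might infer that the comparison is biased, or that the trial would favour the more harmful formula. The documents do not support this. They give no exit rates by group and never name the analysis set; that only infants reaching full feeding are compared is an inference from the exit rule, the outcome definition and the stated tests. This objection stands, and the point is worded accordingly.

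**The analysis set and missing-data rules belong in the SAP.** True, and their absence is not the point. The exit rule is stated, and it ends participation. A SAP could name an all-randomised set, but it cannot restore intake data that were never recorded.

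**The exit clause can be read more mildly.** It may mean exit only where illness makes continuing unsuitable. It does not say that earlier data are discarded, and sepsis or NEC after full feeding would not remove a value already observed. All this is fair. It lowers the likely number of affected infants but leaves those who exit before full feeding.

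**The plan treats losses as random.** A reader might infer this from the 20% allowance, but the text does not say so. The allowance protects the number of infants, not comparability.

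**The test is not at fault.** Correct: a Mann-Whitney test could include infants who never reach full feeding if a rank were assigned to them. The gap lies in the data and the scoring.

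**The larger scenario is extreme.** Exits of 10% and 30% are roughly 10 and 28 infants (Fisher p about 0.002), an imbalance that would be plain in the participant flow. At 15% and 25% with ρ = 0.3 the false-positive rate is barely above 5%. Part of any loss of power is also the fall in numbers already budgeted: Mann-Whitney power is about 83% with all 95 per group and about 75% with 20% exit unrelated to feeding time.

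**Double blinding.** It limits selective decisions to exit an infant, but not exits caused by the formula itself.

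**Conclusion.** The point holds in a limited form. The exit rule, an outcome that exists only for infants who reach full feeding, and tests on observed values together leave the primary comparison open to selection bias of unknown size and direction. It could be negligible if exits are few, balanced or unrelated to feeding time. With moderate imbalance, a true 7.1-day difference could appear as about 4 to 6 days; with strong imbalance, as little as 2 days or as much as 9.4. These sizes rest on assumed exit rates, lognormal times and correlations of 0.3 to 0.8, none of which the documents give.

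The matter should still be settled in the protocol, because it concerns the only primary outcome and data not recorded after exit cannot be supplied later by the analysis.

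**What to change.** 1. Separate leaving study treatment from leaving data collection, with clinical handling left as it is. Record enteral intake, the date of full feeding and adverse events to discharge for every randomised infant, unless consent for data is withdrawn.
2. Make the primary analysis cover all randomised infants by allocated group: cumulative incidence of full feeding, with death before full feeding as a competing event.
3. Prespecify how discharge before full feeding is handled and add a sensitivity analysis. Simply censoring these infants may itself be informative if they are the slow feeders.
4. Report exits by group and reason.
5. Reconcile two passages: Table 2 allows CPAP on the date of randomisation, while the Exit Criteria list ventilatory support as a reason to leave.

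**Cost.** No extra patients or visits, since discharge is already the study endpoint; data recording continues for infants who would have exited. The primary analysis becomes slightly more complex, and the sample-size basis, now a two-mean formula on 76 per group, must be restated to match.

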**Figure 1 F1:**
[figure not shown]
The overall design of the study.

**Table 1 T1:** Data collection schedule.

	**Staff member**	**T1**	**T2**	**T3**	**T4**	**T5**
Symptom of FI	Neonatal physician	**×**				
Informed consent	Research assistant	**×**				
Contact information	Research assistant	**×**				
Sex	Neonatal physician		**×**			
Gestational age	Neonatal physician		**×**			
Mode of delivery	Neonatal physician		**×**			
Apgar score	Neonatal physician		**×**			
Maternal issues	Neonatal physician		**×**			
Weight	Neonatal nurse		**×**			**×**
Gastric residual volume	Neonatal nurse			**×**	**×**	
Abdominal circumference	Neonatal nurse			**×**	**×**	
Length	Neonatal nurse		**×**			**×**
Head circumference	Neonatal nurse		**×**			**×**
Time to reach total enteral nutrition	Neonatal physician					**×**
Duration of abdominal distension	Neonatal physician					**×**
Duration of vomiting	Neonatal physician					**×**
Length of hospital stay	Neonatal physician					**×**
Cost of hospitalization						**×**
Time of parenteral nutrition	Neonatal physician					**×**
Main serum parameters	Neonatal physician			**×**	**×**	
Incidence of adverse events	Neonatal physician					**×**

*T1 screening; T2 baseline evaluation; T3 beginning of intervention; T4 end of intervention; T5 discharge*.

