### Study Population

Table 2 specifies all inclusion and exclusion criteria.

**Table 2 T2:** Inclusion and exclusion criteria.

Inclusion criteria
• Admission between December 2021 and December 2023.
• Gestational age (GA) <32 weeks or birth weight (BW) <1,500 g, appropriate for gestational age, admitted to Department of neonatology, Children's Hospital of Chongqing Medical University within the first 24 h after birth, maximal enteral intake <50 ml/kg/day
• Patients are fed with PF when HM is not available after admission
• Meet the diagnostic criteria of FI. Currently, a clear and universal definition of FI is lacking, FI is defined as follows with reference to relevant literature (5, 16–18): One or two of the criteria below are met: (1) gastric residual volume ≥50% of the previous feeding volume (≥ two times within 24 h), with the presentation of vomiting and/or abdominal distension; (2) feeding plans fail: including feeding withheld or decrease > 6 h, or not increased >24 h (5)
• Parental consent has been obtained
Exclusion criteria
• Perinatal asphyxia: (1) Apgar score of <4 at 5 min; (2) Fetal umbilical artery acidemia: pH <7.00 and/or base deficit worse than or equal to minus 12 mmol/L; (3) A significant peripartum or intrapartum hypoxic-ischemic event (e.g., uterine rupture, placental abruption, cord prolapse, amniotic fluid embolism, fetal exsanguination from a vasa previa or massive feto-maternal hemorrhage, etc.).
• Potential metabolic or chronic disease, congenital abnormality, or any other diseases that may affect feeding ability, normal growth, and development before recruitment
• Patients who need surgical treatment under general anesthesia (ligation of patent ductus arteriosus is excluded) before or on the date of randomization
• Blood pressure is unstable (allowing for dopamine <5 μg/kg/min)
• Ventilator dependence or FiO2 >40% on the date of randomization (allowing for nasal intubation, CPAP, and/ or oxygen mask)
• Grade III or IV intraventricular hemorrhage is diagnosed before or on the date of randomization

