### Randomization

Randomization will be performed using the SPSS software package (version 22.0) using a random number generator in a 1:1 ratio. A statistician who is not involved in recruitment and subsequent data analysis will generate the randomization list, and the list will be concealed. After random allocation lists have been generated, the allocation group (AAF or EHF) will be stored in sequentially numbered, sealed, opaque envelopes. These envelopes will be opened by a third-party individual at each study enrolment after baseline measures have been obtained.

The study will be double*-*blinded. A nutritionist who is not directly involved in inpatient care will prepare and label the formula with the participant's randomization number, date, and time of feeding, and then deliver the formula to the nurse caring for the infant. The medical and nursing teams caring for the infants will be unaware of the type of formula used for feeding. The trial statistician will perform data analysis and be kept unaware of treatment group assignment until the results are finalized.

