### Feeding Schedule

According to the guideline for nutrition support (19), enteral feeding is started within the first 24 h of life. Human milk is encouraged, and preterm formula is fed when human milk is not available due to the mother's or family's condition. Patients with FI are temporarily fed with AAF (Neocate® Nutricia, London, UK) or EHF (Alfare® Nestle, Netherlands) instead of HM or PF. Nutritional feeds start at 15–20 mL/kg/day and are increased by 20–30 mL/kg/day. The gastric residual volume (GRV) is checked before each feeding. If GRV is ≥ 50% of the previous feeding, then enteral feeding was ceased for 1 h, and patients are reassessed. If GRV is not improved, complete blood count, C-reactive protein (CRP), and abdominal X-rays are performed and assessed. If these results can rule out NEC and severe infection, patients are fed in the same amounts for 2–3 days. Enteral feeding is increased at the same rate until full enteral feeding (150 mL/kg/day) every 3 h is reached. Enteral feedings are withheld: in the presence of bloody or biliary gastric residuals, in cases of abnormal abdominal examination, and/or in cases of abnormal abdominal X-ray. As soon as the residuals, the abdominal examination, and/or X-ray return to normal, feeding is resumed with AAF or EHF at the same speed. Once the patients with FI show clinical improvement, AAF or EHF feeding is discontinued, and the previous feeding, either HM or PF is resumed. When full enteral nutrition is insufficient, all patients receive parenteral nutrition solutions (6), which are gradually decreased with increasing enteral feeding. Other routine treatments for FI are given in the two groups according to the guidelines. Table 3 shows the study formulas. Figure 2 shows the feeding schedule.

**Table 3 T3:** Study formulas.

**Characteristics**	**Study formula**	
	**AAF**	**EHF**
Nutrient density (KJ/100ml)	279	284
Nutrient composition per 100 ml		
Total Protein (g, % calories)	2.0,12%	1.82,11%
Total Carbohydrate (g, % calories)	7.0,42%	7.5,43%
Total Fat (g, % calories)	3.4,46%	3.39,46%
Arachidonic acid (ARA), mg	11.3	8.5
Docosahexaenoic acid (DHA), mg	11.3	8.5
Minerals		
Phosphate (mg/100 ml)	59	46
Calcium (mg/100 ml)	85	68
Iron (mg/100 ml)	1.1	0.7
Osmolarity (mOsm/L)	310	170

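### Exit for sepsis, NEC, ventilatory support or critical illness ends participation, not just study formula, so randomised infants may have no primary outcome value

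*Protocol article*

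**What the plan says.** All references are to the protocol article.

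- **Exit Criteria.** Besides death or discharge before full enteral nutrition and withdrawal by the guardian, the list contains: "Sepsis, NEC, use of ventilatory support, or critical illness is not suitable for continuing to participate in the study".
- **Study Population, Table 2.** One exclusion reads: "Ventilator dependence or FiO2 >40% on the date of randomization (allowing for nasal intubation, CPAP, and/ or oxygen mask". Non-invasive support at entry is therefore acceptable.
- **Feeding Schedule.** Stopping study formula is a normal event in this trial: "Once the patients with FI show clinical improvement, AAF or EHF feeding is discontinued, and the previous feeding, either HM or PF is resumed".
- **Table 1.** The last two time points are distinct: "T4 end of intervention; T5 discharge". The row "Time to reach total enteral nutrition" is marked at T5 only.
- **Primary Outcome.** The measure is "age at the first day of achieving full enteral feedings as the indicator", with full feeding meaning at least 150 mL/kg/day on three consecutive days. The study endpoint, given under Secondary Outcome, is the day of discharge.
- **Randomization.** "The medical and nursing teams caring for the infants will be unaware of the type of formula used for feeding".
- **Sample Size.** "a sample size of 76 per group is required, accounting for a 20% miss rate", which leads to 95 per group and 190 in total.
- **Statistical Analyses.** Continuous outcomes are compared by t-test or Mann-Whitney U test.

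**The concern.** Four clinical events that arise after randomisation take an infant out of the study. Each can come before full enteral feeding, which is the primary outcome. Once participation ends, the article provides for no further observation, so the outcome may never be recorded for that infant.

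Two things are at stake. First, the comparison would rest on infants who avoided these events, not on everyone randomised. The events are plausibly tied to feeding progress: the Background says that delayed full enteral nutrition raises infection risk, and the Discussion suggests that AAF may lower nosocomial infection. Second, each such exit uses up part of an allowance meant for losses of every kind.

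A smaller problem lies in the respiratory trigger. Table 2 separates ventilator dependence from nasal intubation, CPAP and mask. The exit line names ventilatory support with no mode, no threshold and no requirement that it be new or escalated. Two clinicians could treat similar infants on CPAP differently.

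**Working it through.** **1. The plan's own sample size.** Inputs from Sample Size: SD 15.6 days, difference 7.08 days, Zα = 1.96, Zβ = 0.84.

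n = (1.96 + 0.84)² × 2 × 15.6² / 7.08² = 7.84 × 486.72 / 50.1264 = 76.1, stated as 76 per group.

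With 20% loss: 76 / (1 − 0.20) = 95 per group, 190 in total. Both figures reproduce and are not in dispute.

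**2. The allowance for loss.** 95 − 76 = 19 per group; 190 − 152 = 38 in total; 19 / 95 = 20%. This covers every reason for a missing outcome, including death, discharge before full feeding and guardian withdrawal. The documents give no rate for sepsis, NEC, ventilatory support or critical illness after randomisation, and no share of infants on permitted support at entry. None of the 19 can be assigned to the exit line.

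**3. What happens to an infant who meets the exit line.**

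| Step | Source | Result |
|---|---|---|
| Event occurs before full feeding | Exit Criteria | Participation ends |
| Primary outcome recorded | Table 1 | Only at T5, discharge |
| Observation after exit | Not provided for in the article | No assurance that T5 is completed |
| Primary comparison | Statistical Analyses | t-test or Mann-Whitney needs an observed value |

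**4. Whether the outcome could still be observed.** It is an age, read from daily enteral intake, and does not depend on which milk is given. The schedule already expects infants to return to human milk or preterm formula while still in the study, separates end of intervention from discharge, and records the outcome at discharge. An infant who recovers from sepsis or comes off a ventilator and then reaches full feeds in hospital has an outcome that can be recorded with the existing form.

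**5. Entry against exit for respiratory support.**

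| | Entry (Table 2) | Exit Criteria |
|---|---|---|
| Ventilator dependence | Excluded | Covered |
| Nasal intubation, CPAP, mask | Allowed | Not addressed |
| New or escalated support required | Not applicable | Not stated |

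No other section reconciles the two columns.

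**The case against.** **The respiratory wording is probably harmless.** The phrase stands beside sepsis, NEC and critical illness, all serious deteriorations, and the line turns on suitability to continue. A stable infant on CPAP who has just been found eligible would hardly be judged unsuitable for that reason. This largely stands. A reader might infer that infants eligible on CPAP must leave at once, but the text does not require it. On its own, the missing qualifier is a matter of clarification.

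**Handling of data after exit belongs in the full protocol or analysis plan.** This stands in part. The article does not say that data from exited infants are discarded, and analysis sets are properly left elsewhere. But exit criteria are conduct rules, and this one is printed as ending participation. An analysis plan can decide whom to include; it cannot recover feeding data that were not collected.

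**Returning to ordinary milk is described only after improvement.** True, so it is no precedent for managing deterioration. It does show that the outcome is meant to be recorded after study formula has stopped.

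**No effect is shown.** This stands. Two stronger readings are tempting:

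- *A loss of power.* With 95 enrolled per group and losses unrelated to outcome, assumed total losses of 30% to 50% would bring power from about 80% to between 74% and 60%. Those rates are assumptions without support in the documents, and they could not be attributed to this line.
- *Bias in favour of one formula.* The care teams are blinded, so exits should not follow knowledge of allocation. Blinding does not prevent the events themselves from being related to formula or feeding progress, but the documents do not allow a direction to be stated.

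**Conclusion.** The point holds as a design weakness that is cheap to remove. Followed as written, the exit line removes randomised infants for clinical events after randomisation, possibly before the primary outcome is seen, although the design could still capture that outcome at discharge. The mismatch with the entry allowance for non-invasive support is secondary and mostly a matter of wording.

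Its size is unknown. The only relevant figure is the all-cause allowance of 19 per group (20%).

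The conclusion rests on two assumptions: that ending participation means the T5 outcome is not reliably collected, and that some of these infants would go on to reach full feeds before discharge. If the full protocol already keeps exited infants under observation, only the wording change remains.

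**What to change.** Amend the Exit Criteria in two respects.

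1. Make sepsis, NEC, ventilatory support and critical illness reasons to stop study formula only. Keep recording age on the first day of full enteral feeding until discharge, and analyse each infant in the allocated group. Covering all four events matters, since changing the respiratory trigger alone would leave the others ending participation. Guardian withdrawal stays a true exit, and infants who die or are discharged before full feeding will still lack a value.
2. Word the respiratory trigger as new invasive mechanical ventilation, or escalation beyond the support allowed at randomisation. Because Table 2 lists nasal intubation among the allowed modes, name the permitted modes explicitly.

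The cost is a short amendment and continued recording of routine feeding data after formula is stopped. No visit or measurement is added, because Table 1 already records the outcome at T5. The statistical price is some dilution of the difference between formulas, since infants who stop early have had less of the allocated product. The sample size need not be recalculated on this account, as the documents give no rate from which to do so.
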